#### Allocation

Random allocation will be achieved using Research Randomizer [12]. The participants will be randomised into two, equal sized block groups. The sequence will be concealed in opaque envelopes until the interventions are assigned. A member of the research team will be responsible for enrolling participants and implementing the randomisation process. The participants will not be blinded. The assessors and data analysts will be blinded to which group the participants are allocated to.

### Intervention

Intervention group participants will undergo an individual, unsupervised 12-week strength and conditioning program which aims to improve strength and endurance of the musculature around the joints identified above. Exercise instructions are detailed below and will use mostly elastic resistance bands [13]. The program will require three repetitive sets for each exercise as this has been demonstrated to produce the most effective strength gains [14]. The program will be undertaken three days per week, which lies in an optimal training range [14]. The sets and repetitions for each exercise are based on novice and intermediate endurance training [15]. The length of the program is based on results that have shown a significant change in muscle strength and size after a 12-week exercise regime [16] (Table 1). It should be noted that this particular study focussed on a free-weight training program, but 12-week programs have been used with TheraBand resistance previously and are documented in the literature [17, 18]. The intensity of the exercises can be progressed by shortening the band or changing to a higher resistance band, and thus increasing the demands of the activity. Where exercises do not use elastic bands, the load can be progressed through increasing the duration of the exercise.

**Table 1 Tab1:** Exercise program parameters

Parameter	
Tempo	3-s eccentric, 1-s hold, 3-s concentric (3–1-3)
Repetitions	15
Intensity	13/20 Rate of Perceived Exertion (RPE) [37]
Sets	3
Rest	1 min
Frequency	3 days per week
Duration	12 weeks

#### Feasibility study

We conducted an initial feasibility study around the design of region-specific exercises that hypothetically strengthen and improve the endurance of the at-risk anatomical areas of the shoulder, wrist and low back described above. Video clips and written instructions for each exercise of the protocol were developed and are described below. These will be supplied to the participants.

#### Instructions for participants

These exercises will be in addition to any regular exercise regime. An exercise diary will be completed by those in the active and controls groups. Furthermore, they will be required to report the dates and duration of their specific exercises below in an exercise diary provided, in order to monitor and keep record of compliance.

### **A. SHOULDER EXERCISES:** (Additional file 1) [19–21]

Due to the complexity of the shoulder joint and surrounding musculature, different exercise sessions will be prescribed for the shoulder training. This method aims to activate different muscles during each session and target shoulder strength as a whole.

### Session 1

#### Exercise 1. Internal rotation/external rotation

External rotation: Standing upright, attach the resistance band to a secure object at waist level. Grasp the resistance band tightly in one hand, elbow bent to 90 degrees, and shoulder turned inwards. Rotate the lower arm slowly outward against resistance as far as you can go without pain, hold for one second. Slowly return to start position and repeat. For internal rotation, being in a shoulder turn out position and perform this action in the opposing direction.

#### Exercise 2. Scapulothoracic wall slide

Tie the resistance band together to make a small loop around the wrist/forearm, stand with feet about 5 cm from the wall and forearms parallel on the wall. Keeping elbows at shoulder width apart creating tension by flaring wrists. Slowly slide your forearms up the wall as far as possible, then slowly back to start position.

### Session 2

#### Exercise 1. Push-ups

With different hand location (elbows close to body, elbows at 45 and elbows at 90) hand positioned at shoulder height. **Note:** If you cannot perform push-ups on your toes, then begin by having your knees on the ground.

#### Exercise 2. Latissimus pulldowns

In a seated position, the arms are held overhead at full extension, grasping the resistance band connected to a fixed object, the movement is initiated by pulling both elbows down and back, and completed by slowly returning to the initial position.

### Session 3

#### Exercise 1. Shoulder press

Stand with the centre of the band under your feet and one end in each hand. Bend the elbows and position the hands just above shoulder height. Push your hands above your head, pause and slowly return to the starting position.

#### Exercise 2. Seated rows

Sit on the floor with your legs slightly bent out in front. Loop the band around the soles of your feet. Start with your arms extended. Pull back with elbows entirely, pause and slowly return to the starting position.

### **B. WRIST EXERCISES:** (Additional file 2) [22, 23]

#### Exercise 1. Wrist flexion

Both exercises 1 and 2 can be performed with filled 600 mL bottles of water or the resistance band.

The back of the forearm is placed flat on a desk while you are seated. Your wrist hangs over the edge of the table as demonstrated in the video. Grasp either resistance band or bottle in a fully extended wrist position, palms facing upwards. Bring your hand up away from the ground into a flexed position, pause and then return to the starting position.

#### Exercise 2. Wrist extension

In the opposite position to the previous exercise, place the front of your forearm on table with wrist in the fully flexed position grasping resistance over the edge of the table. Against resistance and gravity, you are to raise the wrist, pause and then lower to starting position.

#### Exercise 3. Radial deviation

Stand or sit with the resistance band held between your hands. Palms facing up and wrist beginning with knuckles facing inwards. With tension on the band, move your hands away from the middle, pause and then return to the start position.

#### Exercise 4. Ulnar deviation

Stand or sit with the resistance band between hands, palms facing down and knuckles facing inwards. With tension on the band move your hands away from the middle, pause and return to the start position.

#### Exercise 5. Weighted wrist rotations

Use a dumbbell or hammer type object, with weight at one end and grip at the other. Stand or sit with shoulders relaxed, elbows flexed to 90 degrees and the dumbbell or hammer held in front of your body. With the wrist starting so your palm is facing up, rotate your forearm so that your palm then faces down (this will mean turning towards the middle), pause, and then return to the starting position. This can then be performed on the other hand.

### **C. LOW BACK EXERCISES:** (Additional file 3) [24–28]

#### Exercise 1. Crab walk

Stand with feet shoulder width apart with knees bent between 30 and 45 degrees. Loop the band around your ankles. Take a wide step sideways, applying tension to the band. Bring your trailing leg so you are in the original position and repeat for 15 steps. Repeat in the process in the opposite direction.

#### Exercise 2. Lunge

Stand with one foot on the middle of the band. Keeping your elbows bent, grip the ends of the band and hold at chest level. Place your opposite leg behind you, with your knee slightly bent. Keeping your trunk straight, bend your front knee lowering your body downwards, pause, slowly return to the original position and repeat.

#### Exercise 3. Deadlift

Stand in the middle of band with both feet about hip-width apart. Squat down, grasp ends of band and take up slack. Keep elbows and back straight and extend hips to slowly return from the squat to an upright position, pause and return to starting position.

#### Exercise 4. Back extension

Lay down on your front with your hands underneath your shoulders and elbows tucked in neatly at your side. Using your arms for a small of assistance extend your lower back by lifting your head and chest off the ground, pause and then slowly lower yourself back to the ground.

### Control group

The group participating in the strength and conditioning protocol will be compared to a control group. These participants will be required to walk briskly 3 times a week for 30 min for the duration of the program (12 weeks). This will be in addition to any regular exercise regime. Furthermore, they will also be required to report the dates and duration of their walking on the exercise diary provided, in order to monitor and keep record of compliance.

### Outcomes

#### Primary outcome

##### Injury rate

Measured via a brief questionnaire designed especially for this study, which asks about shoulder, wrist or low back pain. It will ask for information about the pain frequency, duration, intensity, if the pain began while practising their manual therapy skills, and if they were in the role of ‘doctor’ or ‘patient’ at the time. Self-reported region specific numerical rating scales are included to measure pain intensity [29]. The questionnaire will ask if this has impacted their ability to continue to practice their skills or their Activities of Daily Living (ADLs). It will be administered at the beginning and every 4 weeks during the trial, i.e. 3 times over 12 weeks. The questionnaire will be completed online at weeks 4 and 8, with SMS reminders sent to participants in these weeks.

#### Secondary outcome

##### Muscle Strength and endurance

One-repetition maximum (1RM) will be estimated via submaximal strength testing procedures. Grip strength will also be measured via a validated and calibrated dynamometer [30, 31]. These measurements will be performed at the beginning of the trial and repeated at the end.

### Data collection

#### Baseline measures

A questionnaire will be given to each participant to obtain demographic information, establish the amount they practise their manual therapy skills, and note any previous related injuries. A self-administered short form, the International Physical Activity Questionnaire (IPAQ), will also be completed in order to gain information on participant’s physical activity over the previous 7-day period. The IPAQ and manual therapy practise questionnaire will then be completed every 4 weeks to assess any change in injury status, including contemporary injury in the preceding 4 weeks and the impact that injury may be having on the participant.

Baseline maximal strength of muscle groups will be estimated using the multiple repetition test procedure (5–10 submaximal strength test) instead of a traditional 1RM test. In this test the maximum amount of repetitions measured for a particular load will be used to estimate the 1RM from the formula 1RM = load (kg)/(1.0278–0.0278 x reps) [32]. A 1RM will be calculated for strict shoulder press, bench press, seated row, Latissimus Dorsi pull down, deadlift, and back racked lunge. Participants will be instructed on correct use of equipment prior to the testing session and given time to familiarise themselves with the equipment. A general warm-up will be completed consisting of 2 min of low-intensity indoor rowing and of low-intensity indoor cycling. This will be followed by specific warm-up of 10 min of dynamic stretches incorporating movements that work through the range of motion required for the lifts to be tested [33]. The participants will be instructed to perform a warm-up set of 5–10 repetitions with a light load and given a 1 min rest period. Thereafter, 3–5 separate single attempts will be performed. Subjects will lift a weight initially 40–60% of the perceived 1RM. The increments of weight are dependent upon the effort required for the lift. The weight added will become smaller as the effort to lift the weight increases. If subjects can perform more lifts than designated by the testing protocol, they will be allowed a minimum of four minutes’ rest and then reassessed. Participants will be instructed to perform each exercise to acute muscular exhaustion or form fatigue. Any repetitions not performed with a full range of motion will not be used. When the subject can only lift the weight five to ten times, that weight and the number of repetitions will be recorded and used to estimate the 1RM.

Grip strength dynamometry will be performed during the strength testing procedure. Participants will be given two attempts to familiarise themselves with the device. Then they will perform three attempts on each side with a 30-s rest between each. The highest measure will be taken for each hand [30, 31]. Fig. 1 provides a schedule of enrolment, interventions, and assessments.

**Fig. 1 Fig1:**
[figure not shown]
Schedule of enrolment, interventions, and assessments

#### Data management

Data will be stored on a password-protected laptop and completed paperwork kept in a locked filing cabinet for 5 years. Paperwork will be shredded and data sets will be deleted after this time.

#### Statistical analysis plan

Descriptive statistics for demographic and outcome data will be based on frequency distributions for categorical data and means and standard deviations or medians, interquartile ranges, and ranges for continuous data, as appropriate. Univariate analysis for treatment group comparisons will include χ^2^ and Fisher exact tests for categorical comparisons, and t-tests or non-parametric Mann-Whitney *U or Wilcoxon signed rank* tests for continuous outcomes. After adjusting for baseline measures, changes in injury rates and muscle strength and endurance over the course of the study will be compared between groups using repeated measures ANOVA or linear mixed models, depending on the final dataset. Data will be analysed using IBM SPSS version 24.0 (Armonk, NY) and *p*-values < 0.05 will be considered statistically significant. The IPAQ results will be used as a covariate in the analysis.

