**Methods:**

This study will involve a prospective cohort of chiropractic students who are currently learning manual therapy at an undergraduate level. Participants will be eligible for inclusion if they are enrolled in 3rd or 4th-year chiropractic manual therapy units at Murdoch University chiropractic course. The intervention group will follow a 12-week strength and conditioning program comprised of preventative exercises that address each body region previously identified as being prone to injury. The control group will complete a 12-week walking program. The primary outcome is injury rate, measured via a short questionnaire. The secondary outcome will be strength, measured via submaximal strength tests.

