#### Exclusion criteria

Potential participants will be excluded from this study if they are currently suffering from musculoskeletal pain in the shoulder, neck or low back region or have done so in the past 3 months or have a reported chronic physical disability.

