#### Sample size

Based on an approximate and conservative baseline injury rate of 30% (0.3) derived from a comprehensive review [1, 5], a sample size of *n* = 212 (*n* = 106 per group) will have 80% power to detect a decrease in injury rate of 50% to an injury rate of 15% (0.15) in the treatment group (alpha = 0.05, beta = 0.2).

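### The trial is powered on the proportion injured, but the plan puts injury rates into a linear change-over-time model chosen after the data are in, and names no single primary analysis

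*Protocol article*

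**What the plan says.** The abstract states: "The primary outcome is injury rate, measured via a short questionnaire". The Sample size section treats this outcome as a proportion of participants: 212 students, 106 per group, 80% power, and a "decrease in injury rate of 50% to an injury rate of 15% (0.15) in the treatment group" ("alpha = 0.05, beta = 0.2").

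The Statistical analysis plan section offers two routes for this outcome.

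- **Univariate:** chi-square and Fisher exact tests for categorical data. For continuous outcomes it lists t-tests, Mann-Whitney or Wilcoxon signed rank tests, all under treatment group comparisons.
- **Adjusted:** after adjustment for baseline measures, "changes in injury rates and muscle strength and endurance over the course of the study" are to be "compared between groups using repeated measures ANOVA or linear mixed models, depending on the final dataset", with IPAQ as a covariate.

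Neither route is called primary. The threshold is p < 0.05.

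The Exclusion criteria bar anyone "currently suffering from musculoskeletal pain in the shoulder, neck or low back region or have done so in the past 3 months". The primary outcome questionnaire asks about shoulder, wrist or low back pain at the start and then every 4 weeks over 12 weeks.

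**The concern.** There are three difficulties.

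1. **Model and outcome do not match.** A design sized on injured or not injured is handed to models for continuous data, in the same sentence as strength. Those models suit strength. No binary repeated-measures model is offered for injury.
2. **The contrast is unclear.** In repeated measures ANOVA, comparing change over time between groups is usually the group-by-time test. That test asks whether the gap between groups differs from one questionnaire to the next. The trial's question is whether fewer students are injured. Shoulder and low back pain are excluded at entry, so for two of the three outcome regions there is little baseline to change from.
3. **The deciding test is open.** The model waits on the final dataset, and the univariate test stands beside it.

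A real halving of injuries could therefore be missed, or the main p-value could come from whichever analysis is preferred once the data are known.

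A smaller slip sits in the same section. The signed rank test is a paired test and does not compare two independent groups. It is listed for continuous outcomes, so it bears on strength and not on the primary outcome.

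**Working it through.** **Inputs.** Proportions 0.30 and 0.15, alpha 0.05, beta 0.2 and 106 per group (Sample size); 1:1 allocation (Allocation); reports at the start and every 4 weeks to week 12 (Primary outcome).

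**Step 1: the plan's own figure.** Pooled two-proportion formula, mean proportion (0.30 + 0.15)/2 = 0.225:

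n per group = [z_a √(2 × 0.225 × 0.775) + z_b √(0.30 × 0.70 + 0.15 × 0.85)]² / 0.15²

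- Two-sided: [1.960 × 0.5906 + 0.8416 × 0.5809]² / 0.0225 = 120.5, so 121 per group (242).
- One-sided: 95 per group (190).
- One-sided with continuity correction: 108 per group (216).

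None gives exactly 106. The nearest is one-sided with continuity correction, a variant the plan does not state. What matters here is that the figure comes near a comparison of two independent proportions, and that no repeated-measures element appears in the stated basis.

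**Step 2: power of the matching test at 106 per group, two-sided.**

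Φ[(0.15 × √106 − 1.960 × 0.5906) / 0.5809] = Φ[(1.544 − 1.157) / 0.581] = Φ(0.666) = 74.7%.

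**Step 3: what the group-by-time test sees.** Assume a constant risk in each 4-week window and independent windows. The window risks are then

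- control: 1 − 0.70^(1/3) = 0.112
- intervention: 1 − 0.85^(1/3) = 0.053

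The gap is about 0.059 at each of weeks 4, 8 and 12. A constant gap is no interaction, so a test over those three reports should reject in about 5% of trials even though injuries are halved. Adding a zero baseline creates an interaction, but it is diluted over four time points.

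**Step 4: simulation.** 106 per group, 30% against 15% over 12 weeks, two-sided 0.05, 3,000 trials per setting (Monte Carlo standard error at most √(0.25/3000) = 0.9 points). Two kinds of dependence between reports were tried: a random intercept on the logit scale (SD 0, 1 or 2), and persistence of an injury to the next window (none, or half).

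| Test | Random intercept | Persistence |
|---|---|---|
| Any injury over 12 weeks, two proportions | 74–76% | 74–76% |
| Group main effect over the three follow-up reports | 78–79% | about 70–78% |
| Group-by-time, weeks 4, 8 and 12 | about 5–6% | about 5–9% |
| Group-by-time, zero baseline added | 20–45% | about 15–40% |
| Group-by-time, equal non-zero baseline added | 17–35% | not run |

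With no true effect (random intercept SD 1), the tests rejected in about 4% to 5% of trials.

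**The case against.** The strongest reply is that the section never names a group-by-time test. It says the groups will be compared after adjustment for baseline, and a group effect averaged over follow-up is a permissible reading. That effect keeps about 70% to 79% power, close to the cumulative test. This stands, so the low figures are conditional on how change is read. It does not settle the matter, because the text does speak of changes over the course of the study.

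Second, a test that matches the powered endpoint is in the plan. This also stands: a reader who concluded that the powered comparison is absent would be wrong. The defect is that it is listed only as univariate, with nothing to say whether it or the model decides.

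Other stronger readings go further than the document allows.

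- *A linear model on injured/not injured gives no valid risk difference, or inflates false positives.* A linear model on 0/1 data does estimate a difference in proportions per report, and the simulation shows no inflation for a single pre-fixed test. It does not directly give the 12-week contrast of 30% against 15%.
- *There is no baseline at all to adjust for.* Wrist pain is not an exclusion, and practice amount, IPAQ and previous injuries are also collected at baseline.
- *Repeated measures ANOVA will lose 27% of participants.* That figure is 1 − 0.9³ and needs an assumed, independent 10% missing at each of three reports. The document gives no such rate, and the mixed model named in the same sentence keeps partial data.
- *The open choice means results will be picked.* The choice may only concern missing or unbalanced data, and the Allocation section says analysts are blinded to group. Blinding reduces the risk of a data-driven choice without removing it.

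Finally, injured/not injured is inferred from the Sample size section, since the Primary outcome section also collects frequency, duration and intensity of pain. The sample size nevertheless commits the trial to a proportion.

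**Conclusion.** The point holds in this form: the outcome is powered as a proportion, its adjusted analysis is a normal-theory model of change picked once the dataset is final, and no analysis is designated primary. These are rules the article states, not detail left to a fuller document.

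Under the group-by-time reading, power falls from about 75% to about 5–9% over the follow-up reports, or to about 15–45% with a near-zero baseline. Under the main-effect reading there is little or no loss. The figures rest on a constant hazard and on assumed persistence or correlation, none of which the document gives; the ordering was the same in every setting tried. The harm lies in possible loss of power, an unclear estimand and an open choice of test, not in the false-positive rate of any one test fixed in advance. Because the primary outcome is affected, it should be corrected before data are seen.

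**What to change.** Before any outcome data are seen:

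1. **Primary analysis.** Name one: the proportion with at least one new injury over the 12 weeks, compared between groups by a binary-outcome model (for example logistic or modified Poisson) adjusted for baseline IPAQ. Report a risk difference or risk ratio with 95% CI. State what counts as new, in particular for a student with wrist pain at entry.
2. **Secondary analysis of the 4-weekly reports.** Use a logistic GEE or logistic mixed model, and test the group effect over follow-up rather than the group-by-time term.
3. **Strength.** Keep linear models with baseline adjustment for strength only.
4. **Deletions.** Remove the data-dependent choice of model for the primary outcome, and remove the Wilcoxon signed rank test from the between-group comparisons.

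The cost is a change of wording and slightly more analysis work, with no extra data collection. It does not cure the sample size: the cumulative test has 74.7% two-sided power at 106 per group, and 121 per group would be needed for 80%. That is a separate matter.
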